## Introduction

 Hypertensive disorders of pregnancy (HDP) affect approximately 10% of pregnancies worldwide and are among the leading causes of maternal and fetal morbidity and mortality, contributing to approximately 14% of maternal deaths every year.^1 2^ Early prediction and diagnosis would facilitate targeted surveillance, which would improve allocation of resources for healthcare providers and avoid unnecessary hospital attendance for patients. Traditional antenatal surveillance includes blood pressure and urinalysis at every visit, which identifies HDP at the time of manifestation.^3^ Recent advancements in first-trimester combined screening, such as with the Fetal Medicine Foundation (FMF) algorithm, have improved risk assessment for the development of pre-eclampsia, which facilitates effective preventative interventions such as daily aspirin from the first trimester.^4^ The introduction of soluble fms-like tyrosine kinase-1 and placental growth factor (PlGF) as diagnostic triage tools in symptomatic women has aided clinical decision making in admission and treatment of women with suspected HDP.^5^,^7^ There remains no effective tool that aids continuous and dynamic risk assessment of HDP throughout pregnancy in asymptomatic women, which would allow for a personalised care plan and improved mitigation of the severity of disease and complications.

Uric acid has been implicated in oxidative stress, inflammation and endothelial dysfunction and, therefore, proposed as a useful biomarker and treatment target in neurological, cardiovascular and metabolic conditions.^8^
^9^ In pregnancy, uric acid has been proposed as a pathogenic, diagnostic and predictive marker of hypertensive disease, with some studies suggesting salivary uric acid could be used as a surrogate, or even more accurate, marker in hypertensive diseases in pregnancy.^10 11^
12,14 Salivary biomarkers for disease detection and monitoring are a potential tool for a variety of conditions.^15^ Saliva sampling is simple, non-invasive and does not require clinical involvement, making it ideal for remote monitoring. Pilot studies have demonstrated that elevated salivary uric acid in pregnant women correlates with an increased risk of developing HDP.^13^

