### Objectives

To assess the efficacy of the Salurate pregnancy remote self-monitoring system in predicting the onset of HDP. By comparing the Salurate system with traditional screening and diagnostic methods, this study aims to determine the sensitivity, specificity, positive predictive value (PPV) and negative predictive value (NPV) of Salurate in identifying pregnant women who will go on to develop HDP. Additionally, the study aims to evaluate the time-to-diagnosis using the Salurate system in comparison to conventional diagnostic approaches.

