#### Primary objective

To test the hypothesis that the inclusion of the Salurate pregnancy remote self-monitoring system in pregnant women’s care pathway would help to predict the subsequent development of HDP prior to what is currently possible using traditional methods.

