### Recruitment and sampling

This is a prospective, multicentre, observational cohort study spanning two trusts across three sites in south-west London: St George’s Hospital NHS Foundation Trust, Epsom and St Helier University Hospitals NHS Trust. The study schema is shown in figure 5. Women attending their first trimester nuchal scan will have a calculation of their risk of hypertensive disease in pregnancy as per the first trimester combined pre-eclampsia screening algorithm.^17^ If their risk of preterm pre-eclampsia is calculated as greater than 1:300 and they satisfy the remaining inclusion criteria, they will be approached and recruited to undertake weekly remote salivary uric acid testing using the Salurate system until the conclusion of pregnancy, with written consent obtained. Participation involves no additional appointments or travel but could extend the initial clinic visit by up to 30 min. Data on antenatal and perinatal maternal and neonatal outcomes will be collected, and the relationship of test results to outcomes will be analysed by a medical statistician. The study is expected to open in September 2024, will be open to recruitment until December 2025 and will close in June 2026.

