### Inclusion and exclusion criteria

All women aged 16 years old and over with a viable singleton intrauterine pregnancy between 10 and 16 weeks’ gestation at the time of enrolment, a risk of preterm pre-eclampsia of >1:300 as determined by the Aspirin for Evidence-Based Pre-eclampsia Prevention algorithm^5^ and able to provide informed consent will be eligible for recruitment. The algorithm combines maternal factors, mean arterial pressure (MAP), uterine artery pulsatility index (UtA-PI) and maternal serum pregnancy-associated plasma protein-A (PAPP-A) and PlGF at 11–13 weeks’ gestation and is used routinely at recruiting centres. Exclusion criteria: significant comorbidities that will interfere with participation or physical incapacitation from performing self-sampling; presence of serious mental illness, learning disabilities or educational status or language barrier that influences capacity to use the Salurate app or understand the instructions for use; lack of access to a smartphone or internet at home; periodontal disease, gingivitis or oral cancer.

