### Schedule of events

Participants will be approached at their initial visit, and subject to eligibility and consent, will be enrolled in the study. They will be issued a Salurate sampling kit, and a member of the research team will guide the participant through the process of taking a sample and using the Salurate app to upload a picture of their test. Their unique study ID will be registered on the Salurate Clinician Portal and an initial CRF will be completed, recording data on maternal demographics, medical history, obstetric history and data from their first trimester combined pre-eclampsia screening (MAP, PAPP-A, crown-rump length, left and right UtA-PI and risk of preterm pre-eclampsia).

Each participant will submit weekly samples from enrolment until the conclusion of pregnancy. A predictive model algorithm analyses the data supplied by the participants via the Salurate app and provides a prediction with the likelihood of an adverse event (hypertensive disease of pregnancy, FGR) occurring. Several colourimetric measurements are extracted from the uploaded test from the participants, which relate to the concentration of uric acid in the saliva sample. The algorithm looks at the change from week to week, and using the trend from preceding weeks calculates a risk of HDP within a given timeframe. The trend is based on specific patterns of uric acid levels linked with known HDP events learnt from previous trials data. This prediction is calculated post hoc and not revealed to the participant or clinical trial research team. Data on the primary and secondary outcomes will be retrieved from the participants’ medical notes at the conclusion of pregnancy and added to the CRF.

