### Data analysis

The quantitative data for this study will be analysed and reported according to the relevant reporting guidelines.^16 21^ All analyses will be performed in StataSE V.16.1 statistical analysis software. All clinical primary and secondary outcomes (maternal and neonatal) will be presented across the whole cohort as percentages with 95% CIs. Missing outcomes data will be presented. Women’s characteristics at enrolment into the study will also be presented with percentages or summary statistics as appropriate.

Salivary uric acid concentration (Salurate) observations will be presented graphically over time from the initial 10–14 weeks pregnancy record through to the end of study participation (1) for the whole cohort, (2) by primary outcome (HDP present or absent) and (3) for each secondary outcome, including adverse maternal or perinatal outcomes. Numbers and percentages of missing Salurate reports will be presented by week of pregnancy with the number of women participating in the study as the denominator (which may vary in the last weeks of the study depending on when they give birth). This will be used to assess the degree of compliance of women to the testing regimen. No multiple imputation or other forms of missing data replacement will be used to estimate missing values of Salurate. No missing data replacement will be employed for clinical outcomes or participant’s characteristics at enrolment, and every effort will be made to record these data. We anticipate that rates of data missingness will be low.

A mixed-methods analysis of longitudinal data will be used to determine the relationship between Salurate results and the primary and secondary outcomes in this cohort. The Salurate algorithm will be employed, and its sensitivity, specificity, PPV and NPV to identify the primary outcome will be presented with 95% CIs. We will also determine how soon the primary outcome would be indicated using Salurate results and compare this with traditional prediction methods such as the FMF algorithm or National Institute for Health and Care Excellence (NICE) checklist. Subgroup analyses will explore whether the Salurate algorithm has greater diagnostic value in particular women according to baseline characteristics, although these analyses may not have enough statistical power to be definitive.

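### The planned 'how soon' comparison with the FMF algorithm cannot inform the primary objective, because every participant is recruited on a first-trimester combined screen that precedes any Salurate alert

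*Protocol article*

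**What the plan says.** The primary objective is to test whether Salurate would help to "predict the subsequent development of HDP prior to what is currently possible using traditional methods". The general Objectives refer to comparison with traditional screening as well as diagnostic methods, and add an aim to "evaluate the time-to-diagnosis using the Salurate system in comparison to conventional diagnostic approaches".

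The one timing analysis described under Data analysis is to determine "how soon the primary outcome would be indicated using Salurate results and compare this with traditional prediction methods such as the FMF algorithm"; the sentence then adds the NICE checklist as a second example.

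Entry depends on a first-trimester screen. Recruitment and sampling states that women whose risk of preterm pre-eclampsia "is calculated as greater than 1:300 and they satisfy the remaining inclusion criteria, they will be approached and recruited". Inclusion and exclusion criteria requires "a risk of preterm pre-eclampsia of >1:300 as determined by the Aspirin for Evidence-Based Pre-eclampsia Prevention algorithm", an algorithm that combines maternal factors, MAP, UtA-PI, PAPP-A "and PlGF at 11–13 weeks’ gestation and is used routinely at recruiting centres". The Introduction describes "first-trimester combined screening, such as with the Fetal Medicine Foundation (FMF) algorithm", so the named comparator is the same class of test as the entry test.

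On Salurate, Schedule of events states: "Each participant will submit weekly samples from enrolment until the conclusion of pregnancy". The algorithm works on week-to-week change and the trend over preceding weeks.

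**The concern.** A comparison of how early two methods indicate disease is informative only if either could come first. Here one of them is a one-off test done before enrolment, and a result above 1:300 on a test of that kind is the condition for being in the cohort. The other cannot report until some weeks of samples have accumulated. The sign of the difference appears to be settled by the design.

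This matters because the sentence is the only timing analysis in the Data analysis section, and the primary objective is about timing. Taken literally, the result would show Salurate later than FMF in every woman. If the rule for what counts as an FMF indication were chosen after the fact, the result would depend on that choice and not on the biomarker. Neither outcome would tell a reader whether Salurate gives useful warning or adds to what is already known at 11–13 weeks.

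**Working it through.** **The plan's own figure.** The sample-size section gives N = 4000 and about 11.5% prevalence for the composite of HDP, SGA or FGR, and gestational diabetes. Events = 4000 × 0.115 = 460. The 95% half-width for sensitivity s is 1.96 × √(s(1 − s)/460):
- s = 0.50: 1.96 × √(0.25/460) = 0.046, against a stated ±5%.
- s = 0.90: 1.96 × √(0.09/460) = 0.027, against a stated ±3%.

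The stated precision reproduces. The present point does not depend on it.

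**Step 1: order of events.** The risk is calculated at the nuchal scan, women above 1:300 are then approached, and sampling begins at enrolment. The inclusion text allows enrolment from 10 weeks while the screen is at 11–13 weeks, but since the risk result is itself an eligibility criterion, the screen must come first. Call the gestation at enrolment E; the screen result is available at or before E.

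**Step 2: earliest Salurate alert.** If k weekly samples are needed, the earliest alert is at E + (k − 1) weeks. The article requires a trend, so k is at least 2, but it does not state k. Assuming k = 2 to 4:

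| k | Earliest alert | Best possible lead over the entry screen |
|---|---|---|
| 2 | E + 1 week | −1 week |
| 3 | E + 2 weeks | −2 weeks |
| 4 | E + 3 weeks | −3 weeks |

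Even at k = 1 the best possible lead is 0.

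**Step 3: the entry screen as a dichotomous test at 1:300.** All 4000 women are test-positive. Sensitivity = 100%, specificity = 0%, Youden index = 1 + 0 − 1 = 0, and NPV = 0/0, undefined. PPV equals the prevalence of the outcome: 11.5% on the composite figure, or 5% to 20% if HDP prevalence is assumed to lie in that range (the article gives no figure for HDP alone).

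**Step 4: a stricter FMF cut-off.** The article names none. Suppose one were chosen. A woman above it was flagged by a test that preceded enrolment, so the lead is still zero or negative. A woman below it is never flagged by FMF, so she has no FMF indication time and the difference is undefined. As illustration, taking the 460 composite events as cases, an assumed FMF sensitivity of 90% to 50% at such a cut-off leaves 460 × 0.10 = 46 to 460 × 0.50 = 230 unflagged. Salurate might find some of these, but that is a gain in detection, not in time.

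**Step 5: accuracy, should FMF accuracy be reported.** Above the entry cut-off FMF keeps some discrimination, but over a truncated range. In a binormal simulation (1.5 million women, 8% outcome, equal variances), an AUC of 0.80 in all women became about 0.66 to 0.70 when only the top 15% to 35% by the same score were kept. None of these inputs comes from the article. The figures illustrate direction and do not estimate an effect in this trial.

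**The case against.** Several counter-arguments have force.

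- **The 1:300 threshold is for eligibility.** The article never says that crossing it indicates HDP. It concerns preterm pre-eclampsia, whereas the primary outcome is all HDP, including gestational hypertension. The rule for an indication could sit in the full protocol or SAP. This stands as far as it goes, but no rule defined later can undo selection on the comparator's class of test or make a pre-enrolment test report after enrolment. At any cut-off the contrast is non-positive or undefined.
- **FMF is only an example, and the NICE checklist is named beside it.** This stands. NICE is not the entry test, and nothing in the article makes it positive in every participant. A reader might extend the argument to all the traditional prediction methods; the text does not support that.
- **The entry algorithm is named after the aspirin prevention trial, not FMF.** Equating the two rests on the Introduction and on the description of the entry test. At the least, both are first-trimester combined screens.
- **No FMF accuracy contrast is planned.** This stands. Data analysis plans sensitivity, specificity, PPV and NPV for Salurate alone. A reader might infer that the trial would make Salurate look better than FMF through selection. The article describes no such head-to-head, and better ranking within the enrolled women would be a true statement about those women. Only extrapolation to unselected women would be wrong.
- **Time-to-diagnosis is already an aim.** This stands too. The Objectives name it, and the article may leave its computation elsewhere. But the sentence that Data analysis does contain is a different comparison.

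**Conclusion.** The concern holds for the timing comparison with the FMF algorithm. At the only cut-off the article gives, the FMF-type screen has flagged 4000 of 4000 women before a Salurate alert is possible, by 1 to 3 weeks if two to four samples are needed. At a stricter cut-off, unflagged women have no FMF time to compare. The contrast therefore cannot support the part of the primary objective that concerns predicting HDP earlier than traditional methods.

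This rests on two readings: that the FMF algorithm and the entry algorithm are the same class of first-trimester combined screen, and that a test indicates HDP when its result crosses a cut-off.

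It should not be read as saying that FMF has no discrimination in this cohort. That is true only at the entry cut-off; as a continuous risk, or at a stricter cut-off, it retains some. Nor does it undermine the accuracy analysis of Salurate, which remains estimable, conditional on a risk above 1:300. For that reason this is a should-fix matter and not a threat to the study.

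**What to change.** Rewrite the sentence in Data analysis as follows.

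1. **Timing.** In women with HDP, lead time = gestational age at clinical diagnosis minus gestational age at first Salurate alert. Report the median with CI and the proportion alerted before diagnosis. This serves the time-to-diagnosis aim in the Objectives. Read it alongside specificity at the same alert threshold, since a threshold that alerts freely lengthens lead time.
2. **Added value over first-trimester screening.** Replace the FMF timing comparison with a model for HDP containing the continuous first-trimester risk (for example on the log-odds scale), with and without the Salurate output, and report the change in AUC with CI. Because Salurate output accrues over time, fix the gestation at which it is taken, among women not yet diagnosed. State that the result is conditional on a risk above 1:300 and does not extend to unselected women.
3. **Comparators.** Keep the NICE checklist as a comparator of accuracy. Make no claim of indicating HDP earlier than FMF.

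The cost is mainly wording. The risk of preterm pre-eclampsia is already on the initial CRF and outcomes come from the medical notes; the one thing to confirm is that the date of HDP diagnosis is captured. Sample size, recruitment and care are unchanged, and since predictions are computed post hoc and not disclosed to participants or the research team, the change can be made before results are seen. The downside is that an earlier-than-FMF claim is given up.

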### Patient and public involvement

A range of patient and public involvement activities including surveys and focus groups with women and clinicians have guided choice of participant population, software and test device design. Specific input has been provided by the Action on Pre-eclampsia Charity (APEC). Patient Faced documents were shared with APEC members (consent forms, information leaflets and device designs) and feedback was provided by the service users approached by the charity.

## Ethics and dissemination

Approval has been obtained from Cambridge East Research Ethics Committee (REC reference 24/EE/0123), Medicines and Healthcare products Regulatory Agency (CI/2024/0038/GB) and Health Research Authority (IRAS ID 337290). Participants will be allowed adequate time to read the patient information sheet (PIS) and make a decision about participation in the trial. There are no anticipated disadvantages in taking part in the trial, beyond the potential oral discomfort and 5 minutes a week of the participants’ time to obtain the sample and upload the results to the app. Participation in the study does not alter the participants’ schedule of care. Participants will be provided with information on how to contact the research team in the event of questions, adverse events or withdrawal from the study, both via the PIS and the Salurate app, with no implication of withdrawal on participants’ clinical care.

The results of this study will be published in peer-reviewed journals and presented at national and international conferences. The data obtained by this study will contribute to the design of future studies prior to the approval for clinical use.
